#### BOLD-fMRI data analysis

The fMRI data preprocessing and comparison will be performed using SPM12 software (http://www.fil.ion.ucl.ac.uk/spm/) based on MATLAB 2018a (Mathworks, Inc., USA). The steps including: format conversion, slice timing correction, head motion correction, spatial standardization, linear trend removal, spatial smoothing, and band-pass filtering. After pre-processing, the amplitude of low frequency fluctuation and regional homogeneity will be calculated to reflect the local cerebral functional activity, and the seeds-based functional connection analysis will be performed to reflect the functional integration of the brain. ANOVA will be used for comparisons between the two groups, with multiple comparison corrections.

Furthermore, the *Pearson* correlation analysis will be conducted to assess the associations between the changes of fMRI and the improvement of clinical symptoms.

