### MRI data acquisition

The resting-state fMRI (RS-fMRI) will be performed at the baseline and the end of treatment, respectively. Patients will be asked to do not drink tea, coffee, or alcohol, avoid strenuous exercise, and ensure adequate sleep before the scan.

Patients will undergo RS-fMRI scan with a 3.0T MR scanners (Siemens 3T Tim trio, Erlangen, Germany) at the West China Hospital of Sichuan University. Patients will be asked to stay awake and to keep their heads still during the scan, with their eyes closed and ears plugged. Scans will be performed with the following procedures: localizer, three-dimensional T1-weighted imaging (3D-T1WI), blood oxygenation level-dependent fMRI (BOLD-fMRI) and diffusion tensor imaging (DTI) sequence. The 3D-T1WI scanning parameters will be as follows: repetition time (TR) = 6.008 ms, echo time (TE) = 1.7 ms, data matrix = 256 × 256, field of view (FOV) = 256 × 256 mm^2^. The BOLD-fMRI scanning parameters will be as follows: 31 contiguous slices with a slice thickness of 5 mm, TR = 2000 ms, TE = 30 ms, FOV = 240 × 240 mm^2^, Matrix = 64 × 64, flip angle (FA) = 90°, total volumes = 240. The DTI data will be acquired using a single-shot echo planar image sequence with the following parameters: FOV = 256 × 256 mm^2^, TR = 8500 ms, matrix = 128 × 128, slice thickness = 2 mm with no gap. Two diffusion-weighted sequences were acquired using gradient values b = 1000 s/mm^2^ and b = 0 s/mm^2^ with the diffusion-sensitizing gradients applied in 64 non-collinear directions.

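### The listed fMRI steps name no removal of motion or tissue signal, and the brain-symptom correlation is unadjusted, so residual motion that changes with neck pain could create a spurious association

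*Protocol article*

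**What the plan says.** In the protocol article, the BOLD-fMRI data analysis section assigns pre-processing and comparison to SPM12. It opens its list with "The steps including: format conversion" and continues with "slice timing correction, head motion correction, spatial standardization, linear trend removal, spatial smoothing, and band-pass filtering".

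The outcome measures follow directly. Two are local indices (low-frequency amplitude and regional homogeneity) and the third is connectivity from seed regions. For the arms, "ANOVA will be used for comparisons between the two groups, with multiple comparison corrections". A Pearson analysis is then to "assess the associations between the changes of fMRI and the improvement of clinical symptoms".

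No covariate is named for either the ANOVA or the correlation. The only other safeguard against motion is in MRI data acquisition, where patients are asked to "keep their heads still during the scan, with their eyes closed and ears plugged". Scans take place at baseline and at the end of treatment.

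**The concern.** Head motion correction in its usual sense realigns the volumes. It leaves in the time series the intensity changes that motion has already caused. Detrending and smoothing do not remove them. Band-pass filtering removes only what lies outside its band: at a repetition time of 2 s the highest resolvable frequency is 1/(2 × 2) = 0.25 Hz, so faster physiological fluctuation folds back and may fall inside the band. A correction for multiple comparisons controls chance findings and does nothing about a confounder.

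The exposed analysis is the third aim in the Background, the link between symptom improvement and change in brain activity. It relates two changes that both occur after randomisation, so randomisation does not protect it. Patients enter with neck pain above 4 out of 10 and are scanned again after treatment. It is plausible, though the article does not say so, that the ability to hold the head still changes with neck pain. If it does, and motion signal remains in the data, the fMRI measures and the VAS can move together with no neural link.

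**Working it through.** **Inputs from the protocol article.** MRI subsample of 20 per arm, stated minimum of 15 per arm, 20% dropout (Sample size). Pilot VAS reductions of 2.86 and 2.14, SD 0.99 (Sample size). Two-sided 0.05 (Clinical data analysis; used here as the nominal level for the correlation). TR 2000 ms, 240 volumes (MRI data acquisition).

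**Assumed inputs.** a is the correlation of motion change with pain relief and b is the correlation of motion change with fMRI change. The article gives neither. The range taken is 0.3 to 0.7 for each, plus a = 0 as the no-link case.

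**Step 1: the plan's own MRI figure.** 15/(1 − 0.20) = 18.75, rounded up to 19. The stated 20 fits, since the text also allows for unusable data. After 20% dropout, 20 × 0.80 = 16 per arm, or 32 in all.

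**Step 2: size of the spurious correlation.** Let M be standardised motion change. Let pain relief be P = aM + √(1 − a²)·e₁ and fMRI change be F = bM + √(1 − b²)·e₂, with e₁ and e₂ independent, so there is no true brain-pain link. Then corr(P, F) = ab. The partial correlation given M has numerator ab − a·b = 0.

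**Step 3: false-positive rate of one Pearson test.** 20,000 simulated trials per cell. The article does not say whether the arms are pooled, so one arm of 20 is shown as well.

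| a / b | ab | N = 40 | N = 32 (20% loss) | N = 20 (one arm) |
|---|---|---|---|---|
| 0 / any | 0 | 0.05 | 0.05 | 0.05 |
| 0.3 / 0.3 | 0.09 | 0.084 | 0.079 | 0.065 |
| 0.5 / 0.5 | 0.25 | 0.353 | 0.278 | 0.188 |
| 0.7 / 0.7 | 0.49 | 0.909 | 0.835 | 0.614 |

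Fisher-z check at N = 40, where √(40 − 3) = 6.083:

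- r = 0.09: 0.0902 × 6.083 = 0.549, and Φ(0.549 − 1.96) + Φ(−0.549 − 1.96) = 0.079 + 0.006 = 0.085.
- r = 0.25: 0.2554 × 6.083 = 1.554, and Φ(1.554 − 1.96) = 0.34.

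Both agree with the simulation.

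**Step 4: after adjustment.** With motion change partialled out, the rate lies between 0.047 and 0.055 in every cell. This assumes that motion is measured without error and acts linearly.

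**Step 5: the randomised arm comparison.** The assumed VAS difference is (2.86 − 2.14)/0.99 = 0.73 SD. Carried through motion it becomes 0.73ab. At 0.5/0.5 that is 0.73 × 0.25 = 0.18 SD, with upper-tail rejection of 0.083 at 20 per arm against 0.025 under no effect. Over the assumed range it runs from 0.07 to 0.36 SD, with upper-tail rejection from 0.040 to 0.202.

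**The case against.** The strongest objection is that this is a condensed journal article. The section gives no filter band, smoothing kernel, seed regions or correction method, and nuisance regressors could be seen as settings of the same kind. The list is also introduced by a word that leaves it open. A reader might infer from it that motion and tissue signal will certainly stay in the data. The document does not support that: it shows that removal is not specified, not that it will be omitted, and reading head motion correction as realignment alone is an interpretation. What remains is that the chain is itemised down to format conversion and detrending, and the test that follows is a stated plain Pearson correlation. A team following those steps literally would do no nuisance regression. The clinical analysis section, by contrast, does name covariates for its model.

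The second objection is that the pain-motion link is conjecture. It is: the article holds no motion data, and with no link the error rate stays at 5%. A reader might infer that motion will fall as pain falls, but nothing in the document establishes it.

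A reader might also infer that the more effective arm would necessarily show a false brain difference. That goes too far. It needs motion to differ between arms after treatment, and even at 0.5/0.5 the induced difference is 0.18 SD.

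Finally, change in motion is measured after randomisation. If treatment alters it, adjusting the arm comparison for it may remove part of a real effect or introduce bias. That objection stands and shapes the fix.

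**Conclusion.** The point holds in a limited form. As listed, the pipeline names no regression of motion or of white-matter and CSF signal, and the brain-symptom correlation is unadjusted, so its result could not be separated from a motion artefact. The size is conditional on assumed correlations. At N = 40 the false-positive rate of a single test is about 5% with no link, 8% at 0.3/0.3 and 35% at 0.5/0.5; at the 32 patients left after the planned dropout, the last two are 8% and 28%. The bias may therefore be negligible or substantial, and the document cannot tell which.

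The concern falls mainly on the mechanistic correlation. It is secondary for the randomised fMRI comparison and does not touch the primary VAS outcome. It is worth correcting because the remedy is cheap, and because fixing it in advance closes a choice that could otherwise be made after the results are seen.

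**What to change.** 1. In the BOLD-fMRI data analysis section, add regression of the head-motion parameters and of the mean white-matter and CSF signals, carried out before the local measures and seed connectivity are computed.
2. Replace the plain Pearson test with a partial correlation of fMRI change and clinical improvement, given change in mean framewise displacement.
3. Report motion by arm and visit.
4. Keep the randomised group ANOVA without the post-treatment motion covariate as the main comparison. Show the motion-adjusted version, and any exclusion by a preset framewise-displacement limit, as sensitivity analyses.

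No new data are needed, since realignment already yields the motion parameters. Nuisance regression costs some temporal degrees of freedom: even a 24-parameter motion set with two tissue signals is 26 regressors against 240 volumes. The partial correlation costs one residual degree of freedom, 37 in place of 38 at N = 40. Exclusion by motion belongs in a sensitivity analysis because 20% dropout already leaves 16 per arm against the stated minimum of 15. Losing two more patients in an arm would leave 14, and each change score needs two usable scans.

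### Regional homogeneity is computed on spatially smoothed data, so part of the measured local synchrony comes from the smoothing kernel and the measure loses validity and sensitivity

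*Protocol article*

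**What the plan says.** The BOLD-fMRI data analysis section of the protocol article describes one pre-processing chain. It ends, and the derived measures begin, as follows: "linear trend removal, spatial smoothing, and band-pass filtering. After pre-processing, the amplitude of low frequency fluctuation and regional homogeneity will be calculated". ALFF and ReHo therefore share one input, and that input has been smoothed. ReHo is not exempted from the smoothing step, and no later smoothing of the ReHo maps is mentioned. The third measure uses the same data: "the seeds-based functional connection analysis will be performed to reflect the functional integration of the brain". No kernel width is given.

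The same section sends the imaging measures into a between-group ANOVA and into Pearson correlations of fMRI change with clinical improvement. The Sample size section sets the scanned subsample at 20 patients per group.

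**The concern.** ReHo is Kendall's coefficient of concordance across the time series of a small block of adjacent voxels. Gaussian smoothing replaces each voxel by a weighted average of its neighbours, so adjacent series come to share content even when the underlying signals are unrelated. The quantity being measured is then partly produced by the processing. ALFF describes the amplitude within each voxel and does not have this problem in the same way, so one shared order does not suit both.

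At stake are the second and third aims in the Background: the change in brain activity, and its relation to symptom improvement. ReHo is one of three named fMRI measures serving those aims. If much of its value comes from the kernel, a ReHo finding is harder to read as local neural synchrony, and real differences may be pushed towards the ceiling of 1.

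**Working it through.** The protocol states no figure on this point, so there is none to reproduce. The check is a simulation of the stated order.

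**Inputs from the MRI data acquisition section**
- In-plane voxel, from "FOV = 240 × 240 mm^2^, Matrix = 64 × 64": 240 / 64 = 3.75 mm.
- Slices: "31 contiguous slices with a slice thickness of 5 mm". The acquired voxel is therefore 3.75 x 3.75 x 5 mm.
- Time points: "total volumes = 240".
- Repetition time: 2 s, from "TR = 2000 ms, TE = 30 ms".

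**Assumptions, not in the article:** kernel 4, 6 or 8 mm FWHM; pass band 0.01-0.08 Hz; 27-voxel neighbourhood; and, as an alternative to the acquired grid, a 3 mm isotropic grid.

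**Formula.** With K = 27 series, T = 240 time points, R_t the sum of ranks at time t, and S = Σ(R_t − mean R)²,

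W = 12 S / [K²(T³ − T)].

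For unrelated series the expected value is 1/K = 1/27 = 0.037. W relates to the mean pairwise rank correlation r by W = [1 + (K − 1) r] / K, so r = (27W − 1)/26.

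**Step 1: independent Gaussian noise, smoothed, band-passed, then W**

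| Grid | None | 4 mm | 6 mm | 8 mm |
|---|---|---|---|---|
| Acquired, 3.75 x 3.75 x 5 mm | 0.04 | 0.06 | 0.17 | 0.32 |
| Assumed 3 mm | 0.04 | 0.13 | 0.33 | 0.50 |

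Repeat runs moved these values by about 0.01. On the acquired grid, 8 mm gives r = (27 × 0.32 − 1)/26 = 0.29 between voxels that share nothing. On the 3 mm grid it gives (27 × 0.50 − 1)/26 = 0.48.

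**Step 2: resampling.** Interpolating noise from the acquired grid to 3 mm also mixes neighbours. With no smoothing, W is then already about 0.12 to 0.19, depending on the interpolation. It rises to about 0.37 to 0.57 after 6 to 8 mm. If the data are resampled this way, the kernel multiplies W by about three (0.37/0.12 = 3.1; 0.57/0.19 = 3.0), less than the 3 mm row of the table suggests.

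**Step 3: true differences.** A single shared signal carried 0.2 or 0.4 of the variance, and mean W was compared.

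| Grid | None | 4 mm | 6 mm | 8 mm |
|---|---|---|---|---|
| Acquired | 0.219 vs 0.421 | 0.368 vs 0.572 | 0.703 vs 0.865 | 0.893 vs 0.951 |
| Difference | 0.202 | 0.204 | 0.162 | 0.058 |
| 3 mm | 0.225 vs 0.388 | 0.636 vs 0.831 | 0.903 vs 0.961 | 0.970 vs 0.988 |
| Difference | 0.163 | 0.195 | 0.058 | 0.018 |

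At 4 mm the contrast is not compressed. At 6 to 8 mm it is.

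**Step 4: standardised differences.** Spread shrinks along with the means, so the raw contrasts in step 3 overstate the loss. Two groups were simulated on the 3 mm grid with shared-signal fraction 0.20 versus 0.25 and between-subject SD 0.05.
- Spatially uniform signal: 0.85 with ReHo on unsmoothed data; 0.83, 0.80 and 0.76 with smoothing first at 4, 6 and 8 mm. At 8 mm the loss is 1 − 0.76/0.85 = 11%.
- Locally correlated signal (9 mm): 1.06 against 1.00, 0.80 and 0.66. At 8 mm the loss is 1 − 0.66/1.06 = 38%.

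**The case against.** The strongest reply has four parts.

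- **Loose wording.** A condensed article uses one sentence for three measures, and its step list is introduced in non-exhaustive terms. Handling specific to ReHo may sit in the full protocol. This stands only in part: whatever the order within the list, smoothing is named as pre-processing and ReHo is placed after pre-processing. That is a stated order, not a silence. If the imaging team already works differently, only the sentence needs correcting.
- **Size.** The effect depends on an unstated kernel and grid, it is small at 4 mm on the acquired grid, and resampling alone lifts the floor. All of this stands, and the figures are given as ranges for that reason.
- **Group bias.** A reader might infer that smoothing first creates a spurious difference between the arms. The documents do not support that: the same pipeline serves both arms and both scans, so under the null there is no bias in a known direction.
- **Motion.** A reader might also infer from the step list that motion and tissue-signal regression are absent and that residual motion will mimic a treatment effect. The article lists head motion correction and is silent on the rest. Such detail is commonly left to a fuller document, and nothing in the text ties motion to pain. It is not part of this point.

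**Conclusion.** As written, the order is unsuitable for ReHo and should be changed. Under the stated assumptions, smoothing first raises the concordance of pure noise about four- to eightfold at 6 to 8 mm on the acquired grid (0.17/0.04 and 0.32/0.04), and about threefold once resampling to 3 mm is allowed for. The consequence is a less valid and less sensitive ReHo measure, and a weaker basis for its correlation with symptom change. The simulated loss of standardised difference is 2% to 6% at 4 mm (1 − 0.83/0.85; 1 − 1.00/1.06). At 6 to 8 mm it is 6% to 38%, from 1 − 0.80/0.85 to 1 − 0.66/1.06, depending on how local the signal is. These are simple signal models, so they show direction and rough size, not the loss this trial will see. The point is confined to one of three fMRI measures in the 20-per-group subsample. The primary VAS comparison is unaffected.

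**What to change.** Split the pipeline by measure in the BOLD-fMRI data analysis section:

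- **ReHo:** leave smoothing out of pre-processing, compute ReHo on the unsmoothed, detrended, band-pass-filtered data, then smooth the ReHo maps before group statistics.
- **ALFF and seed-based connectivity:** keep smoothing before the measure is computed, as now.

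State the kernel width and the voxel size after normalisation alongside, so that the residual effect of interpolation on ReHo can be judged.

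The cost is one changed processing script. No new scans or patients are needed, and any ReHo maps already made can be recomputed from the stored images. The change should be fixed before the imaging results are examined by group.

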**Methods:**

This is a randomized controlled trial; 86 patients will be randomly assigned into two acupuncture treatment groups at a ratio of 1:1. The whole study period includes 2 weeks baseline, 2 weeks treatments, and 12 weeks follow-up (4 and 12 weeks after treatment). The pain severity, the neck disability index, the cervical range of motion, and the pressure pain threshold, etc., will be used to evaluate the clinical efficacy of two acupuncture prescriptions for NP treatment. The MRI scans will be performed to detect cerebral activity changes of 20 patients in each group. The clinical data and MRI data will be analyzed, respectively. *Pearson* correlation coefficient will be used to evaluate the association between changes of cerebral activity features and improvement of clinical symptoms.

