Advances in neuroimaging techniques have enhanced studies into the central mechanisms of acupuncture as an analgesic in vivo. In the last two decades, many neuroimaging studies have been performed to elucidate the mechanisms of acupuncture analgesia, and achieved gratifying results [15–18]. For example, an fMRI study on migraines found that acupuncture was effective in improving abnormally reduced functional activity in the rostral ventromedial medulla/trigeminocervical complex area of patients [19]. Recently, significant alterations in the brain structure and function of NP patients have been reported by neuroimaging studies. Compared to healthy subjects, NP patients shown decreased functional activity in the left sensorimotor cortex and right temporoparietal junction [20], as well as increased functional connectivity between the right dorsolateral prefrontal cortex and the right anterior insula, which are associated with pain intensity [21]. Based on these findings, neuroimaging techniques appear to be useful tools for investigating the central mechanisms of acupuncture therapy for NP. Therefore, by MRI, this study aims to (1) evaluate the therapeutic effects of different acupoints prescription on NP, (2) investigate the changes in cerebral activity elicited by acupuncture treatment, and (3) analyze the possible correlations between the improvement of clinical symptoms and changes in brain activity, so as to explore the potential central mechanism of acupuncture for NP.

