#### Sample size

This study aims to compare the difference of the clinical efficacy of two acupuncture prescriptions (group A and group B). According to the results of the pilot study, the average reduction of VAS score in group A was 2.86±0.99, and the average reduction of VAS score in group B was 2.14±0.99. According to the formula, $$ n=\frac{2{\sigma}^2}{{\left(\mu 1-\mu 2\right)}^2}\times {\left({\mu}_{\alpha /2}+{\mu}_{\beta}\right)}^2 $$, with *α* = 0.05 (both sides) and 1 − *β* = 0.80 [24]. The sample size of each group was calculated to be 34, considering a 20% dropout rate; the final sample size was set to 43 per group, making the total of 86 in this study.

There is no widely accepted method for sample size calculation in neuroimaging study. Referring to the previous study [25], 15 participants in each group are the smallest size in neuroimaging studies. Considering a 20% dropout rate and the unavailability of data due to various reasons, this study will randomly select 20 patients from each group for MRI scans.

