### Randomization

Randomization will be carried out in two steps: (1) an independent, blinded statistician will generate a random allocation sequence using SPSS 26.0 (IBM, Chicago, IL, USA). The 86 patients will be randomly assigned into group A and group B at a ratio of 1:1; (2) 20 patients in each group will be randomly selected for MRI according to another random sequence. Allocation concealment will be achieved by sequentially numbered, opaque, sealed envelopes.

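### The fMRI group comparison is stated as an ANOVA without baseline adjustment and is not tied to the change between the two scans; adjusting for the baseline map would gain power at little cost

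*Protocol article*

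**What the plan says.** The second aim, in the Background, is to "investigate the changes in cerebral activity elicited by acupuncture treatment". The abstract gives the same purpose: "The MRI scans will be performed to detect cerebral activity changes of 20 patients in each group". Under MRI data acquisition, two scans per patient are planned: "The resting-state fMRI (RS-fMRI) will be performed at the baseline and the end of treatment, respectively".

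The BOLD-fMRI data analysis section fixes the software, the preprocessing steps and the measures: amplitude of low-frequency fluctuation (ALFF), regional homogeneity (ReHo) and seed-based connectivity. The group test is given in one sentence: "ANOVA will be used for comparisons between the two groups, with multiple comparison corrections". Change is named only in the next step, a Pearson correlation for "associations between the changes of fMRI and the improvement of clinical symptoms".

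On numbers, the Sample size section takes it that "15 participants in each group are the smallest size in neuroimaging studies", and then: "Considering a 20% dropout rate and the unavailability of data due to various reasons, this study will randomly select 20 patients from each group". Under Randomization, "20 patients in each group will be randomly selected for MRI according to another random sequence".

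**The concern.** The imaging question is about change and the data are paired, but the group test is not linked to either fact. At least four analyses fit the sentence: the group main effect over both scans, a comparison of end-of-treatment maps, a comparison of change maps, or a group-by-scan model read through its interaction. They differ widely in power. The first dilutes any treatment effect, because the baseline scan cannot carry one. The second ignores the baseline map. None of the four uses the baseline value as a covariate, although it is already collected.

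With about 15 to 20 usable patients per arm, the choice can decide whether a real difference between prescriptions is seen. Leaving the contrast open also allows it to be picked after the maps have been inspected, for three measures. Finally, the second aim includes change produced by treatment within a group, and a purely between-group test does not address that.

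**Working it through.** **The plan's own figure.** The imaging minimum is 15 per arm with 20% dropout: 15 / 0.8 = 18.75, so 19. With a small allowance for unusable scans, the planned 20 per arm is reproduced.

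**Inputs.** From the protocol article: 20 per arm (planned) and 15 (minimum), 1:1 randomisation, imaging subset drawn at random within each arm, two scans per patient, and two-sided 0.05 (stated for the clinical data and used here per test). Assumed, because the article gives neither: a true end-of-treatment difference d = 0.8 SD, and a correlation r between a patient's two scans of 0.3, 0.5 or 0.7. Also assumed: one region, equal SD at both scans, and no expected baseline difference.

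**Formulas.** Power comes from the two-sided noncentral t distribution with noncentrality (effect / SD) × √(n/2). There are 2n − 2 degrees of freedom, less one for the covariate analysis.

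| Contrast | Effect | SD |
|---|---|---|
| Group effect over both scans | d/2 | √((1 + r)/2) |
| End scan only | d | 1 |
| Change (same test as group-by-time) | d | √(2(1 − r)) |
| End scan adjusted for baseline | d | √(1 − r²) |

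**Worked case, d = 0.8, r = 0.5, n = 20** (√(20/2) = 3.16):
- Over both scans: 0.4 / √0.75 = 0.46; noncentrality 1.46; power 30%.
- End scan only: 0.8 / 1 = 0.80; noncentrality 2.53; power 69%.
- Change: 0.8 / √1 = 0.80; noncentrality 2.53; power 69%.
- Baseline-adjusted: 0.8 / √0.75 = 0.92; noncentrality 2.92; power 81%.

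**Power over the assumed correlations, d = 0.8:**

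| n per arm | r | Both scans | End scan | Change | Baseline-adjusted |
|---|---|---|---|---|---|
| 20 | 0.3 | 33% | 69% | 55% | 73% |
| 20 | 0.5 | 30% | 69% | 69% | 81% |
| 20 | 0.7 | 27% | 69% | 89% | 93% |
| 15 | 0.3 | 26% | 56% | 43% | 60% |
| 15 | 0.5 | 23% | 56% | 56% | 68% |
| 15 | 0.7 | 21% | 56% | 78% | 84% |

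Relative to the change test, the noncentrality of the pooled group effect is √((1 − r)/(1 + r)): 0.73, 0.58 and 0.42 at r = 0.3, 0.5 and 0.7.

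**Checks.** Simulation with 20,000 runs at n = 20 and d = 0.8 gives 33%, 30% and 27% for the pooled effect, 69% for the end scan, and 55%, 70% and 89% for change. The covariate formula ignores the small loss from chance baseline imbalance and is slightly optimistic: at d = 1.0 and r = 0.5, simulation gives 94.1% against 94.5% by formula for n = 20, and 84.5% against 86.2% for n = 15. With no true difference, every test rejects in about 5% of runs.

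**Effect of stricter thresholds.** At a per-test level of 0.001 (n = 20, d = 0.8, r = 0.5), power is 3% for the pooled effect, 17% for the end scan, 17% for change and 28% with baseline adjustment. The ordering holds, but all levels are low.

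**The case against.** The strongest reply is that the sentence never says what the ANOVA is run on. A two-group ANOVA on change maps fits it, and so does a two-by-two group-by-scan ANOVA read through its interaction. The aim, the two scans and the use of change in the correlation all point towards such a reading. This is also a condensed article, and the second-level imaging model may be set out in a document not shown. This stands as far as it goes: a reader might infer that the protocol tests something other than change, but the text neither says nor excludes this.

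A reader might also infer that the null hypothesis is wrong or that false positives rise. The document does not support that for the comparison between arms. Patients are randomised and the imaging subset is drawn at random within each arm, so the expected baseline difference is zero. If the prescriptions do not differ, all these contrasts have expectation zero and reject at about 5%. Chance baseline imbalance is already within that 5%; it costs precision.

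Nor can it be said in general that most of a real difference would be missed. That describes the pooled main effect, and nothing shows that the investigators mean to use it. The end scan alone equals the change test at r = 0.5 and beats it at r = 0.3.

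What the reply does not remove is that no baseline adjustment is named, and that adjustment has the highest power of the four contrasts at every correlation tried.

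**Conclusion.** The point holds as a limited one. The stated group test names no baseline adjustment and is not tied to the change between scans, although change is the declared question and the baseline map is available. Error rates are sound; power and precision are what suffer.

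Under the stated assumptions, with 20 per arm, baseline adjustment gains about 4 to 24 percentage points over the end scan alone and about 18 to 4 points over change as r goes from 0.3 to 0.7. Against the pooled group effect the gain is about 40 to 66 points, but only if that reading were used. These figures are for one region without correction and rest on assumed values of d and r. Under whole-brain correction absolute power is much lower, so the fix improves the analysis without making the imaging comparison well powered. The imaging part is mechanistic and the primary outcome is the pain score, so this point does not touch the main efficacy result. It is worth correcting because it is cheap.

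**What to change.** Before unblinding, replace the ANOVA sentence with one that names a single main contrast. Preferred: compare the groups on the end-of-treatment ALFF, ReHo and connectivity values with the patient's own baseline value as covariate, voxelwise by script or on regional values. Where a voxelwise covariate is not practical in SPM12, use the group-by-time interaction instead. Apply the multiple-comparison correction to the chosen contrast. State that the group main effect over both scans will not be interpreted as a treatment effect. Report within-group change separately for the second aim.

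No extra scans or patients are needed. The adjusted analysis costs one degree of freedom and a little scripting; the interaction avoids the voxelwise covariate but gives up some power. If a fuller analysis document already names the contrast, it should be checked against this and cited.
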